### Study design and aims

2.1

This is a stepped-wedge prospective mixed methods study exploring the feasibility of EWRRS, which is an interactive, multimodal screening program to support the early identification of potential patients who may progress from mild or moderate to severe or critical illness. The detailed study aims:

1.To improve the detection of early signs of clinical deterioration of COVID-19 patients and provide real-time data to the entire clinical team, thus improving team situation awareness of patient deterioration.2.To provide timely and efficient treatment suggestions for COVID-19 patients through the rapid response system, thereby promoting active management of deterioration, stabilizing patient conditions early and avoiding the progression of deterioration to a more serious degree.3.To reduce the workload and risks of occupational exposure of medical personnel during the epidemic through interactive, multimodular processes.4.To identify the COVID-19 progression patterns and characteristics through big data analysis, thus providing an example of EWRRS for future outbreaks of public health events. Moreover, such a system can potentially be extended for use as a grading EWRRS, to respond to deteriorating patients outside of an ICU setting.

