### Study population and setting

2.2

Patients are eligible for this study if they were diagnosed with COVID-19 according to the New Coronavirus Pneumonia Prevention and Control Program (7th edition), published by the National Health Commission of China.^[5]^ Inclusion criteria comprise the following: adult patients (18 years or older) with clear epidemiological history; fever and/or respiratory symptoms; normal or decreased white blood cell count and/or lymphocyte count; high degree of suspected imaging characteristics of novel coronavirus pneumonia; positive results of SARS-CoV-2 nucleic acid detection and serum-specific antibodies; ability to provide a signed informed consent form. Patients were excluded if known life expectancy was less than 48 hours, pregnant or lactating, diagnosed with end-stage diseases, or in immunosuppression states.

Clinical Classification of the COVID-19 patients is according to their disease severity upon admission: *Mild cases*: The clinical symptoms are mild and no pneumonia manifestations can be found in imaging. *Moderate cases*: Patients have symptoms such as fever and respiratory tract symptoms, etc. and pneumonia manifestations can be seen in imaging. *Severe cases*: Adults who meet any of the following criteria: respiratory rate ≥30 breaths /min; oxygen saturation ≤ 93% at a rest state; arterial partial pressure of oxygen (PaO_2_)/oxygen concentration (FiO_2_) ≤ 300 mm Hg; patients with > 50% lesion progression within 24 to 48 hours in lung imaging. *Critical cases*: Adults who meet any of the following criteria: occurrence of respiratory failure requiring mechanical ventilation; presence of shock; other organ failure that requires monitoring and treatment in the ICU.

*Hospital discharge criteria*: normal body temperature for more than 3 days; significantly improved respiratory symptoms, that is, no oxygen supplementation requirement, stable and normal vital signs for longer than 1 day; lung imaging showing obvious absorption and resolution of acute infiltrates; negative results of the nucleic acid test for SARS-CoV-2 two times consecutively, with at least a 1-day interval between tests.

Patient recruitment duration will last for a year, from September 2020 to August 2021. During the study period, patients diagnosed with COVID-19 will be directly admitted or transferred to Beijing Ditan Hospital, which is the government designated COVID-19 hospital.

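### As written, the imaging entry criterion excludes every patient who is mild on admission, although mild patients are part of the stated target and of the mild/moderate class.

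*Protocol article*

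**What the plan says.** Section 2.2 of the Protocol article gives the entry criteria as one list separated by semicolons. It opens: "Inclusion criteria comprise the following: adult patients (18 years or older) with clear epidemiological history; fever and/or respiratory symptoms". It goes on to blood counts, then to imaging, "high degree of suspected imaging characteristics of novel coronavirus pneumonia", and ends: "positive results of SARS-CoV-2 nucleic acid detection and serum-specific antibodies; ability to provide a signed informed consent form".

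The next paragraph of section 2.2 sets out the severity classes and when they are assigned: "Clinical Classification of the COVID-19 patients is according to their disease severity upon admission". For mild cases it says: "The clinical symptoms are mild and no pneumonia manifestations can be found in imaging". For moderate cases it asks for symptoms and adds that "pneumonia manifestations can be seen in imaging".

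Elsewhere mild patients are treated as part of the study. Section 2.1 describes the programme as supporting early identification of "potential patients who may progress from mild or moderate to severe or critical illness", and the closing paragraph of the Introduction gives the same target. The Introduction requires twice-daily self-reports from mild and moderate cases. Section 2.3 assigns recruited patients to three classes, the lowest of which pools mild with moderate. Section 2.4 makes change in clinical classification the primary outcome and the proportions in each severity type a secondary outcome.

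**The concern.** The entry list and the mild definition sit in adjacent paragraphs and pull in opposite directions: one asks for pneumonia-type imaging, the other for its absence. If both are applied as they stand, the patients with the mildest disease never enter, while the aims, the self-reporting rule and the class labels all assume that they do.

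What is at stake is who the results describe. The primary outcome is movement between severity classes, so the baseline mix of classes determines which transitions can be observed. If the pooled lowest class holds only moderate patients, a reader who sees a result for mild/moderate cases will take it to cover mild disease when no mild patient contributed. If staff instead admit some mild patients despite the criterion, the baseline mix depends on judgements that the protocol neither describes nor records.

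**Working it through.** No arithmetic applies: the document gives no figure on this point. The check is to set the stated rules side by side.

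1. **Is the entry list a conjunction?** Three features of section 2.2 say so.
   - The list contains adult age and the ability to give signed consent, both of which must be compulsory.
   - No word marks the items as alternatives to one another; the only and/or wording lies inside single items, such as the symptom item.
   - Where the same section does mean alternatives, in the severe and critical definitions, it says explicitly that any one criterion is enough.

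   The plain reading is that every item is required.

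2. **What does entry then require on imaging?** Findings strongly suggestive of coronavirus pneumonia.

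3. **What does each class require on imaging, and can it enter?**

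| Class on admission (section 2.2) | Imaging in the definition | Compatible with the entry criterion? |
|---|---|---|
| Mild | No pneumonia | No |
| Moderate | Pneumonia visible | Yes |
| Severe | Lesion progression is one of several alternatives | Yes |
| Critical | None stated | Yes |

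   The set of eligible patients and the set of patients mild on admission do not overlap.

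4. **Is there an exemption?** None was found. The Introduction and sections 2.1 and 2.3 refer to mild patients as participants, but none of them says that the imaging item is waived for such patients.

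5. **What happens to the classes used in analysis?** Section 2.2 defines four classes and section 2.3 uses three. Section 2.4 does not say which set the primary outcome uses.
   - With three classes, the lowest is filled at baseline by moderate patients alone. No class is empty, but its label covers a group that is absent.
   - With four classes, mild has no eligible patient at baseline. It can still be reached later, because section 2.3 allows reclassification during treatment and imaging may clear.

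6. **Related text.** The discharge criteria in section 2.2 include "lung imaging showing obvious absorption and resolution of acute infiltrates". This also presupposes infiltrates, which a mild case lacks by definition. It does not show who may enter, but it is a second place where the text of section 2.2 does not fit the mild class.

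**The case against.** The strongest reply is that the list was never meant as a set of joint requirements. Section 2.2 first makes eligibility depend on a diagnosis under the national programme, and the Abstract describes entry simply as adults diagnosed with COVID-19. Exposure history, symptoms, blood counts, imaging and virology could then be diagnostic features that combine by rules in the cited programme, which is not at hand. The list does not state that all items are needed, and the rest of the article takes mild patients for granted. This shows that exclusion was probably not intended. It does not remove the conflict. Nothing in the document says which items are optional, consent stands in the same list, and a recruiter working from this text would have to turn mild patients away.

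A second reply is that little is lost: the moderate part of the aim is untouched, and mild patients may deteriorate less often. The first half stands. The second is plausible but has no figure behind it, and it does not help with a label that claims a group the study did not enrol.

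Some stronger readings are tempting and should not be drawn.

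- **That a whole level of the primary outcome scale is removed.** Section 2.4 fixes no number of levels. On the three-class version no level is empty, and on the four-class version only the baseline value is affected.
- **That the study cannot meet its aim.** The target is mild or moderate illness, and the moderate part remains.
- **That a given percentage of admissions is lost.** The document offers no basis for one.
- **That sites will apply the rule differently.** Section 2.2 describes admission to a single designated hospital, so any inconsistency would be between patients or staff, and the document does not report any.

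**Conclusion.** The conflict is real and lies between two rules that the article states, so it is not a matter of detail left to a fuller document. Applied as written, all patients who are mild on admission, as section 2.2 defines them, fail the imaging criterion. The consequence is limited but material: the pooled mild/moderate class would contain only moderate patients at baseline, and conclusions in the terms of section 2.1 would overreach by the mild part. Progression from moderate to severe or critical illness remains open to study. The number of patients affected cannot be derived from the document.

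This rests on three assumptions: that the inclusion items are all required, which is the plain reading but is not said in so many words; that imaging described as highly suggestive of the pneumonia counts as a pneumonia manifestation in the mild definition; and that entry and admission class are judged on the same imaging. If the first is not what was intended, the list still needs correcting, because its text does not show which items may be absent.

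**What to change.** Reconcile the inclusion list in section 2.2 with the severity definitions, in one of two ways.

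- **Keep mild patients.** Remove pneumonia imaging as an entry requirement and record it at baseline, where it already separates mild from moderate. Section 2.5 already collects imaging as baseline data, so no new procedure is needed. The small downside is a possibly lower deterioration rate per patient.
- **Restrict to patients with pneumonia.** Keep the criterion, and remove mild cases from the target in the Introduction and section 2.1, from the baseline classes in sections 2.2 and 2.3, and from the conclusions. The cost is a narrower population to which the results apply.

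In either case, state in one sentence whether every item of the inclusion list is required. The discharge item on infiltrates should also be reconciled with the mild definition; how that is done is a clinical matter, and no rule is proposed here. All of this is a change of wording, best settled before recruitment begins because it decides who may enter.

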### EWRRS procedures

2.3

For recruited COVID-19 patients, the EWRRS will perform different levels of assessment for the patient alarm information, offering corresponding treatment recommendations (Fig. 2). The details in EWRRS procedures are as follows:

1.After admission, EWRRS performs an initial assessment of COVID-19 patient disease severity based on past medical history, clinical symptoms, vital signs, and other auxiliary examinations. It then classifies them into 3 clinical classifications: mild/moderate, severe, and critical cases. Similarly, during the subsequent treatment, EWRRS will reclassify patients according to the results of updated patient clinical data, if needed.2.For mild/moderate cases, EWRRS will provide “self-reported vital signs” twice to 3 times per day. During treatment, these cases may present mild abnormalities in vital signs or values in lab tests—chest tightness, shortness of breath, resting SpO_2_ less than 95% etc.; these will be regarded as “lower level warning” by the system. The system will then trigger a warning for nursing intervention, with treatment recommendations. These include “Increase frequency of SpO_2_ monitoring (every 4 hours),” “Oxygen therapy via nasal cannular,” and “Dietary and psychological support.”3.Cases where patient symptoms and lab values grow worse and meet the following standards: shortness of breath on exertion (e.g., getting out bed to bathroom); no symptom relief after 1-hour oxygen therapy via nasal cannular; SpO_2_≤95% with any oxygen therapy (nasal cannular or oxygen mask); respiratory rate ≥25/min with any oxygen therapy (nasal cannular or oxygen mask); ROX≤4.88 with any oxygen therapy (nasal cannular or oxygen mask). These worsening symptoms will be identified as “higher level alarming” by the system. Meanwhile, these patients will be reassessed as severe cases. The system will synchronously trigger a warning for physicians to intervene. As a result, these severe cases will receive more monitoring of SpO_2_, blood artery gas check and various intensive respiratory supports according to their PaO_2_/FiO_2_, a blood gas parameter that reflects oxygenation status.4.For severe cases—PaO_2_/FiO_2_ of ≥300 mm Hg; 200 to 300 mm Hg; and 150 to 200 mm Hg—treatment recommendations become “continue oxygen therapy,” “high-flow nasal cannula oxygen therapy, observe 2 hours,” and “noninvasive ventilation, observe 2 hours,” respectively. If these cases continue to deteriorate—altered mental status presented, severe cardiac arrhythmias, shock, airway obstruction, patients with PaO_2_/FiO_2_ <150 mmHg—they will be reevaluated as critical cases by the system; a treatment recommendation of “Call ICU consultation” would then be offered.

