EWRRS is equipped with a complete data processing and evaluation system; it evaluates cut-off values for a variety of clinical parameters. An alarm module setting, applied to coronavirus pneumonia clinical signs/symptoms and clinical severity classifications, will warn when test measures are in excess of cut-off values, predicting when patient condition is becoming more severe. The alarm includes 2 levels, a lower level of warning and higher level of alarming. For instance, critical warning starts when heart rate and blood pressure fluctuate more than 20% from baseline. The lower warning level means oxygen saturation from pulse oximetry (SpO_2_) is more than 2% lower than 93%. If SpO_2_ further decreases, even with supplemental oxygen, it implies that the patient may have a severe course of the disease. The higher level of alarming then will be triggered. As a result, treatment recommendations can be made by physicians and nurses according to patient risk classification and warning level, considering the individual hospital's situation and capacities. These recommendations may include increasing the frequency of monitoring, change of oxygen therapy, advancing respiratory therapy, or transfer of patients to ICU. EWRRS can determine the classification and interactive evaluation of patient information based on the application of 3 different scenario modules—patient, nurses, and physician (Fig. 1): *Patient-driven data evaluation module.* Once admitted, each patient will be requested to log into this system via a predesigned smartphone app. Next, the system will prompt patients to enter their demographic information; it then will guide the self-evaluation and documentation of signs and symptoms under physician order. Subsequently, physicians will provide initial assessment, clinical classification and offer preliminary treatment recommendation according to patients’ current medical conditions. For mild/moderate cases, at least 2 daily self-reports of vital signs are required. The system will offer professional feedback, including suggestions on treatment and recovery to patients. *Nursing-driven data evaluation modul*e. The system will automatically load patient self-reported information, which becomes part of medical record, into this module. If there is any identified abnormal data from vital signs and lab tests, or overdue self-reporting, the system will trigger a warning for nursing to intervene. This could include close observation, more frequent monitoring, dietary management, and/or psychological support, etc. *Physician-driven data evaluation module*. Similar to the nursing data entry module, this module will include all of the key administrative clinical data relevant to that person, including demographics, nursing and physician progress notes, medical problems, medications, lab tests, and results from various diagnostic exams. The system will integrate all the information to identify patients with abnormal clinical presentation, project the disease progression, and provide a priority list of patients that require physician attention. According to different levels of notice (warning or alarming), physicians will decide if more frequent clinical monitoring, checks on blood gas, and alternative therapies are required. After these interventions, the system will reevaluate patients’ updated clinical data, reclassify patients, and adjust treatment plans if needed. This system will incorporate continuous feedback management: identify–feedback–intervene–evaluate–reidentify.

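### The written standards for the physician alarm contain no room-air trigger, so a silently hypoxaemic patient who is severe under section 2.2 can be alarmed late or not at all

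*Protocol article*

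**What the plan says.** Section 2.2 (Study population and setting) lists criteria for a severe case, any one of which suffices. They include "respiratory rate ≥30 breaths /min; oxygen saturation ≤ 93% at a rest state", and neither limit depends on whether the patient is receiving oxygen.

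Section 2.3 (EWRRS procedures) sets the alarm levels for mild/moderate patients.

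- **Step 2, lower level.** The triggers include "resting SpO_2_ less than 95% etc.; these will be regarded as" a lower-level warning. No lower bound is given. The notice goes to nursing: "The system will then trigger a warning for nursing intervention, with treatment recommendations". The response includes nasal oxygen and "Increase frequency of SpO_2_ monitoring (every 4 hours".
- **Step 3, higher level.** Five standards are listed. Two are symptoms: breathlessness on exertion, and symptoms not relieved after an hour of nasal oxygen. The other three are measured: "SpO_2_≤95% with any oxygen therapy (nasal cannular or oxygen mask); respiratory rate ≥25/min with any oxygen therapy (nasal cannular or oxygen mask", and ROX ≤4.88, also on oxygen only. Meeting the standards brings a physician notice and reassessment as severe. The text does not say whether one standard is enough or all are needed.
- **Step 1.** Later reclassification is allowed: "EWRRS will reclassify patients according to the results of updated patient clinical data, if needed".

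The Introduction describes the levels differently: "The lower warning level means oxygen saturation from pulse oximetry (SpO_2_) is more than 2% lower than 93" percent. It ties the higher level to a further fall despite supplemental oxygen. It also lets physicians act on both levels: "According to different levels of notice (warning or alarming), physicians will decide".

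**The concern.** The Discussion singles out silent hypoxaemia, meaning low oxygen without breathlessness, as the reason for identifying potentially severe cases actively. Symptom standards cannot detect this group, and the measured standards do not apply until oxygen has been started. The room-air reading that makes the patient severe in section 2.2 therefore has no matching physician trigger in step 3.

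What is at stake is patient safety. Under step 3 the alarm brings physician intervention, blood gas checks and respiratory support guided by PaO2/FiO2. The alarm levels that section 2.5 says will be recorded are also affected. The primary outcome is not directly affected, because clinical experts assess the final classification (section 2.4).

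**Working it through.** **Rules as coded.** There is no figure in the protocol to reproduce, so the written rules were applied as logic. Any one step 3 standard was taken to suffice, which is the reading most favourable to the protocol.

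- Severe (section 2.2, the two bedside limits): SpO2 ≤93% or respiratory rate (RR) ≥30/min.
- Higher level (step 3): exertional breathlessness, or no relief after 1 hour of oxygen, or, if on oxygen, SpO2 ≤95% or RR ≥25/min or ROX ≤4.88.
- Lower level (step 2): resting SpO2 <95%, or breathlessness.

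**Grid, no dyspnoea.** SpO2 80–100% is 21 values and RR 12–40/min is 29 values, so there are 21 × 29 = 609 combinations. The severe ones are 14 × 29 (SpO2 80–93%) + 7 × 11 (SpO2 94–100% with RR 30–40) = 406 + 77 = 483.

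| | Severe combinations | Severe without a step 3 alarm |
|---|---|---|
| Room air, as written | 483 | 483 |
| On oxygen, as written | 483 | 0 |
| Room air, with the added trigger | 483 | 0 |

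The first row follows directly from the wording: every measured item needs oxygen and symptoms are set to absent. With the added trigger, no alarm is added outside the 483 severe combinations.

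**Individual courses, no dyspnoea.**

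- (a) 88% on room air gives the lower level. On a cannula at 97% and RR 20, no step 3 standard is met, so the alarm is missed.
- (b) RR 32 and SpO2 96% on room air meet no step 3 standard. The nursing module in the Introduction would give a warning for abnormal vital signs. Once oxygen is started, RR ≥25 fires the alarm, so the effect is delay.
- (c) 94% on room air, then 95% on a cannula, gives the higher level and reassessment as severe, although the patient never met the section 2.2 saturation limit.
- (d) 88% on room air, then 92% on a cannula, fires the alarm. The delay is the time to start oxygen plus up to 4 hours if the next reading follows the schedule.

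Course (c) is thus ranked above course (a), although (a) had the far lower room-air saturation.

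**Does ROX rescue course (a)?** The article does not define ROX. Assume (SpO2/FiO2)/RR and FiO2 of 0.24 to 0.40 on a cannula. Then 97/0.24/20 = 20.2 and 97/0.40/20 = 12.1, both well above 4.88. Even at 96% and RR 24, FiO2 would have to reach 96/(4.88 × 24) = 0.82. The room-air results do not depend on this assumption.

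**If all five standards were required**, no room-air patient could qualify, and the gap would be wider.

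**The case against.** The strongest replies are these.

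- **Fig. 2 holds the algorithm and is not shown.** It may contain a room-air branch. This stands as a limit on the finding, but the text would then need to be brought into line with the figure.
- **Step 2 is meant for mild abnormalities in mild/moderate patients**, so 88% could be read as outside it. The Introduction undercuts this by placing a saturation more than 2% below 93% at the lower level. Leaving step 2 would in any case not meet a step 3 standard.
- **Step 1 could reclassify the patient as severe** under the section 2.2 definitions, and the step 4 recommendations would follow. That is possible, but step 1 states no rule and attaches no alarm, and section 2.2 ties its classification to admission.
- **Physicians have other routes.** The physician module gives a priority list and acts on warnings as well as alarms. This stands: the patient is not necessarily unseen. What is lost is the guaranteed higher-level alarm.
- **Escalating only when oxygen fails is a coherent design**, with tighter limits on oxygen (≤95% and ≥25/min against ≤93% and ≥30/min), and extra physician notices work against the aim of reducing workload. The on-oxygen limits are indeed more sensitive. But the design conflicts with the protocol's own definition of severe and its stated need to find silent hypoxaemia.
- **The grid result is true by construction, and 231 of the 483 combinations (48%) pair RR ≥30 with no breathlessness.** Both points are correct. The count shows that the rule has no exception; it says nothing about how often patients are affected.

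**Conclusion.** The concern holds for the text as written. Without dyspnoea, no room-air value of saturation or respiratory rate that is severe under section 2.2 meets a written step 3 standard (483 of 483 combinations). For low saturation the physician alarm is delayed when SpO2 stays at or below 95% on oxygen. It is missed when oxygen lifts SpO2 above 95%, RR is below 25 and no symptoms appear. For RR ≥30 alone the effect is mainly delay.

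The conclusion concerns this alarm only. It does not say that such patients are never seen by a physician or never classed as severe. It rests on the printed text, since Fig. 2 may differ, and on an assumed ROX formula for the on-oxygen cases. The article gives no figures from which to estimate how many patients are affected. Because the group is one the protocol names as a target and the correction is small, the text should be changed.

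**What to change.** - Add to step 3: *resting SpO2 ≤93% or respiratory rate ≥30/min, regardless of oxygen therapy*, as a higher-level alarm to physicians with reassessment as severe.
- Limit the step 2 saturation warning to values below 95% and above 93%.
- Bring the Introduction's description of the two levels into line, and Fig. 2 if it differs.
- State that any one step 3 standard suffices.

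Two optional additions would help. Before go-live, desk-test the rules across SpO2 and respiratory rate, on room air and on oxygen, with and without dyspnoea, to confirm that worse values never give a lower level. During the study, have EWRRS log automatically any section 2.2 severe criterion met without a higher-level alarm.

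The cost is one trigger line, one floor and aligned wording. The optional log uses data already recorded. The downside is some extra physician notices, all for patients who already meet a section 2.2 severe criterion.
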